### Study Setting and Population

This intervention will be nested within the existing KP program, a nationally scaled program for SWs run by the Centre for Sexual Health, HIV, and AIDS Research Zimbabwe on behalf of the Ministry of Health and Child Care (MoHCC) and National AIDS Council. The program aims to reduce HIV acquisition and transmission via the provision of comprehensive sexual and reproductive health services at mobile and static clinics tailored for KP and supported by peer-led community engagement activities [5]. As of 2023, the KP program services include contraception, syndromic management of sexually transmitted infections, mental health screening and treatment, gender-based violence prevention and referral, HIV testing, initiation of antiretroviral therapy, HIV postexposure prophylaxis, and PrEP. The KP program operates mobile outreach clinics in 14 suburbs across Harare, from which 8 TOPAZ study suburbs were selected. Eligible suburbs needed to have ≥3 pharmacies that have a private area to implement the intervention and were willing to implement the intervention. Consequently, the PrEP-in-pharmacy intervention will be conducted in Glen Norah, Mufakose, Epworth, Glen View, Highfield, Kuwadzana, Mabvuku, and Kambuzuma.

### Pharmacy Selection Process

A mapping exercise will be conducted in the selected suburbs to identify pharmacies that meet the TOPAZ pharmacy criteria. A sensitization process will be used to assess the pharmacy owners’ interest in participating in the study. A total of 3 pharmacies per suburb will be shortlisted, and in instances where there are >3 qualifying pharmacies in a suburb, distance from a neighboring TOPAZ study pharmacy will be considered in the selection of the 3 participating pharmacies to ensure pharmacies are well spaced within the suburbs.

### Design

To achieve aim 1, a qualitative study will be conducted. Aim 2 will involve a cluster-randomized control trial, with suburbs as the unit of randomization. In total, 8 suburbs will be randomized to either standard of care, which is collecting PrEP services from the KP program (*comparison condition*), or standard-of-care KP program PrEP services *plus* the option of pharmacy-based PrEP refills, which includes a financial incentive of a gift voucher for pharmacy products (*intervention condition*). FSWs in the KP program who are newly initiated onto PrEP will be recruited into the TOPAZ study prospectively, and outcomes will be measured at 3, 6, 9, and 12 months after PrEP initiation. Aim 3 will use a mixed methods approach to determine the feasibility, acceptability, and scalability of the PrEP-in-pharmacy intervention.

### Aim 1: Formative Research

#### Overview

Formative research activities will be conducted to ensure that the proposed approach addresses barriers to PrEP retention on both the supply (pharmacy) and demand (SWs) sides. Two key stakeholder groups, the pharmacists and SWs, will be engaged to establish advisory boards. The SW advisory board will ensure that the final intervention design aligns with the needs and preferences of the SWs. The pharmacist advisory board will play a key role in operationalizing the PrEP-in-pharmacy intervention and ensuring it is integrated into routine business operations within pharmacies. Consultative meetings will be held monthly to develop the intervention process (Table 1).

**Table 1 table1:** Qualitative approaches to be applied in the formative research phase of the Together Optimizing PrEP Access in Zimbabwe study implementation.

Group	Method	Interviews, n	Inclusion and exclusion parameters	Contribution
Pharmacy advisory board	Consultative meetings	15	Inclusion criteria Pharmacies that are officially registered Pharmacies located in Harare Available to participate in board meetings during the intervention	Inform intervention development from a pharmacy perspective
SW^a^ advisory board	Consultative meetings	5	Inclusion criteria Enrolled in the KP^b^ program Demonstrating knowledge about PrEP^c^ Residing in Harare Available to participate in board meetings over a 24-month period Exclusion criteria SW intending to move out of Harare during the intervention	Inform development of the intervention from an SW perspective
SW	Semistructured in-depth interview	20	Inclusion criteria Aged >16 years Exchanged sex for money or gifts in the last 6 months^d^	Barriers to PrEP retention Mitigating PrEP-related stigma Using pharmacies for PrEP refills Procedures for using and reporting HIV test results Referral services How to create a welcoming environment
Pharmacy personnel^e^	Semistructured in-depth interview	6	Inclusion criteria Aged >18 years Own or work at a pharmacy in Harare	Perspectives of engaging FSWs^f^ in their shops Attitudes and beliefs about SWs Perceived roles in community-based health provision Relationship with referral facilities and staff Views on the viability of pharmacies as distribution sites for daily oral or other forms of PrEP and HIV tests Which pharmacy personnel would implement intervention Comfort with prescribing PrEP and providing HIV testing Existing facilities within or near the pharmacy that provide HIV testing and counseling
Community leader	Key informant interview	6	Inclusion criteria Aged ≥18 years Work with MoHCC^g^, the City of Harare pharmacy, or organizations that may be impacted by the intervention	Seek reactions on main insights from in-depth interviews Invite input on the proposed pharmacy-based approach Identify potential implementation barriers Facilitating roles they can assume
KP program	Formal meeting	—^h^	Inclusion criteria KP program staff at the front line of outreach	Formal appointments Referral procedure preferences Tracking continuation and missed appointments

^a^SW: sexual worker.

^b^KP: key populations.

^c^PrEP: pre-exposure prophylaxis.

^d^Pharmacy owners and staff.

^e^Not limited to SWs enrolled in the KP program.

^f^FSW: female sex worker.

^g^MoHCC: Ministry of Health and Child Care.

^h^Not applicable.

#### Qualitative Studies

Trained social science researchers will conduct qualitative interviews to solicit insights that can be applied to strengthen the PrEP-in-pharmacy intervention (eg, how and where HIV testing should be conducted, how to identify study participants, and confidentiality and privacy). In-depth interviews (IDIs) will be held with SWs and pharmacy personnel, and key informant interviews will be held with community leaders and policy makers using guided questions summarized in Table 1. All interviews will be audio recorded, but in instances where individuals want to be interviewed but prefer not to be recorded, written note-taking methods will be applied. Analytic notes will be written and summarized for synthesis of information into a report that will be presented to the advisory board and stakeholders. Written informed consent will be obtained from all qualitative study interview participants. A rapid qualitative analysis approach will be used to interpret interviews in real time to facilitate intervention finalization [45]. Taken together, data from IDIs and key informant interviews and formal discussions with advisory board members will be used to develop the PrEP-in-pharmacy intervention protocol.

#### Development of the PrEP-in-Pharmacy Intervention

A workshop including the SW and pharmacy advisory boards, and pharmacists from pharmacies that qualify to implement the PrEP-in-pharmacy intervention, will be held to finalize the intervention protocol. Key outputs will be a detailed intervention protocol that has a (1) feasible implementation plan that has been endorsed by advisory boards; (2) training component for pharmacy personnel on HIV testing, PrEP, stigma reduction, and the referral procedures; (3) training component for KP program staff on how the strategy will be integrated with usual services and a referral plan acceptable to pharmacists and KP program staff; and (4) final structure for the escalating incentive (gift vouchers).

### Aim 2: PrEP-in-Pharmacy Intervention Pilot

#### Overview

A 2-arm pragmatic cluster-randomized trial design will be used to determine whether the addition of pharmacies as an optional PrEP refill collection point increases retention on PrEP among SWs compared to the standard-of-care services offered in the KP program (Figure 3). A 1:1 cluster randomization process will be conducted by a statistician using covariate-constrained randomization [46] in R software (version 4.1.3; R Foundation for Statistical Computing). A public randomization event will be held in which the Community Pharmacists Council, MoHCC, and other key stakeholders will participate. There will be no masking at the cluster level (suburbs), and SWs will be informed of the intervention. SWs newly enrolled in the standard-of-care suburbs will not be explicitly informed about the intervention. This trial is not blinded.

**Figure 3 figure3:**
[figure not shown]
Overview of the pre-exposure prophylaxis (PrEP) in pharmacy intervention implementation strategy. FSW: female sex worker; KP: key populations; REDCap: Research Electronic Data Capture.*Escalating gift voucher structure: month 1 refill=US $5 voucher, month 3 refill=US $6 voucher, and month 6 refill=US $7 voucher.

#### Overview of PrEP Services in the KP Program

The KP program requires verbal consent from SWs to dispense PrEP, which is freely available [5]. MoHCC implementation guidelines include free provider-delivered oral rapid HIV testing at initiation, along with provision of a 1-month supply of PrEP. The first refill provides a 2-month supply of PrEP, followed by 3-month supplies for subsequent refills (Figure 4). Free, provider-delivered oral rapid HIV testing will be offered every 3 months, and in accordance with the national PrEP guidelines, only individuals with confirmed HIV-negative results are offered future PrEP refills [47]. KP program data are collected on paper-based forms for all SWs who initiate PrEP routinely; these are used to generate a unique identification number for the SWs and an associated KP program file, which is essential for PrEP refill collection. People who do not return for refill visits are routinely followed up via phone calls, WhatsApp (Meta Platforms, Inc) reminders, and peer outreach. SWs are offered a US $5 transport reimbursement when collecting their PrEP refills routinely in the program.

**Figure 4 figure4:**
[figure not shown]
The pre-exposure prophylaxis (PrEP) refill schedule used by the key populations (KP) program, in alignment with the Zimbabwe national PrEP refill algorithm. Each PrEP refill is supplied with a US $5 transport reimbursement. Refill months indicated in red highlight where an HIV test is required to receive PrEP.

#### Procedures for the Standard-of-Care Arm

SWs enrolled as part of the TOPAZ study in the standard-of-care arm will initiate PrEP following the KP program standard operating procedures. They will be recruited through the KP program outreach clinics; undergo HIV testing; and if they are HIV negative, they provide verbal consent for PrEP initiation and collection of subsequent refills. At each visit, SWs will receive PrEP plus counseling on the importance of adhering to the prescribed PrEP schedule. PrEP refills will be recorded on standardized paper-based data collection tools, per the KP program standards, and will be analyzed from the program records.

Inclusion criteria for enrollment into the TOPAZ standard-of-care arm are (1) initiated on PrEP through the KP program’s mobile outreach clinics operating in 1 of the 4 standard-of-care suburbs, (2) aged >16 years, (3) having exchanged sex for money in the last 6 months, and (4) providing verbal consent.

All participants will receive a US $5 transport reimbursement at the end of each visit. Participants in the standard-of-care arm will be advised that they can collect PrEP refills from the KP program clinics, following standard procedures. Participation in the intervention will continue for 12 months.

#### Procedure for Those Enrolled Through the PrEP-in-Pharmacy Intervention Arm

FSWs initiated on PrEP through the KP program’s mobile outreach clinics in the intervention suburbs will be informed about the intervention, namely, the opportunity to access PrEP refills either from selected pharmacies within the suburbs or through KP program clinics. In addition, the participants will also be informed that PrEP refills in the pharmacy warrant gift vouchers for the first 6 months of the trial, and no vouchers will be available for the remaining 6 months of the trial. Intervention arm participants initiating PrEP will be given a TOPAZ referral slip, which they can redeem at any participating pharmacy or KP program clinic. The same services provided at standard-of-care sites will be available through the pharmacy, namely, HIV testing, PrEP refills, adherence counseling, linkage to additional services, and the US $5 transport reimbursement in line with the KP program care. In addition, FSWs that opt to refill PrEP-in-pharmacies will be offered an incentive in the form of a gift voucher redeemable for products in the pharmacy wherein the refill was collected. The incentive will continue until month 6 and will escalate in value at each visit. Months 1, 3, and 6 will receive gift vouchers valued at US $5, US $6, and US $7, respectively. To measure retention on PrEP without incentive, participants will not receive a gift voucher in the last 2 refill visits of the intervention, that is, months 9 and 12; however, data will be collected. Implementing pharmacies will be given a TOPAZ study handbook with standard operating procedures for the intervention. In addition, the KP program will conduct weekly support visits to participating pharmacies.

#### Recruitment of FSWs in PrEP-in-Pharmacy Intervention Suburbs

FSWs initiating PrEP will be informed that enrolling as an intervention participant is voluntary and their refusal will not interfere with the KP program standard of care, including their ability to access PrEP. FSWs will also be given information about the intervention and the associated risks in detail. Interested FSWs will be given an information flyer, and consent to participate will be obtained verbally. Information flyers will be available in the 3 main languages spoken in Zimbabwe: English, Shona, and Ndebele. The eligibility criteria to participate in the intervention arm are (1) initiated on PrEP through the KP program’s mobile outreach clinics in 1 of the 4 intervention suburbs, (2) aged >16 years, (3) having exchanged sex for money in the last 6 months, and (4) providing verbal consent to enroll in the TOPAZ study.

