##### Outcome 3: Patronage for PrEP Services at Pharmacies

FSWs (overall) and FSWs (aged between 18 and 24 years) patronage for PrEP services at pharmacies, defined as the proportion of all PrEP refill pickups (1, 3, 6, and 12) in intervention suburbs occurring at pharmacies, overall and by pickup month.

#### Data Analysis for Aim 2

For retention outcomes at 1, 3, 6, 9, and 12 months, the KP program database will be used to compare the number and proportion of FSWs retained on PrEP as defined earlier by study arm. We will conduct an intent-to-treat analysis to estimate the intervention’s effect using a cluster-based permutation test applied to the individual-level binary outcome (retained on PrEP and not retained on PrEP) using the *cptest* function in the R cvcrand package (or a similar function). The permutation test will be conducted with the same covariates used during the constrained randomization process at the suburb level (expanded from the values of the cluster-level covariates, according to which cluster everyone belongs). This approach will be repeated for the other outcomes. To produce a measure of effect, a Generalized Estimation Equations model will also be constructed to generate a risk difference of PrEP retention among people initiating PrEP in intervention versus comparison suburbs and a 95% CI. In accordance with the CONSORT (Consolidated Standards of Reporting Trials) guidelines, unadjusted estimates will be reported, and the preregistered analysis plan at ClinicalTrials.gov will specify an adjusted model in the case of baseline imbalances. Overall, this analysis framework permits causal attribution.

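### The aim 2 analysis population is defined in two conflicting ways, and if only enrolled women are analysed, arm-specific recruitment after open randomization leaves the causal-attribution claim unsupported

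*Protocol article*

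**What the plan says.** All references are to the Protocol article.

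**Allocation.** Aim 2, Overview: suburbs are randomized at a public event and the trial is not blinded. Design: new PrEP initiators are then recruited prospectively.

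**Intervention suburbs.** The intervention-arm procedure says "the participants will also be informed that PrEP refills in the pharmacy warrant gift vouchers for the first 6 months of the trial". The recruitment section adds "FSWs will also be given information about the intervention and the associated risks in detail", and then "Interested FSWs will be given an information flyer, and consent to participate will be obtained verbally". Women are told that "enrolling as an intervention participant is voluntary and their refusal will not interfere with the KP program standard of care", so a woman can start PrEP and decline TOPAZ. The last eligibility criterion is "4) providing verbal consent to enroll in the TOPAZ study".

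**Control suburbs.** The Overview states that "SWs newly enrolled in the standard-of-care suburbs will not be explicitly informed about the intervention". The standard-of-care procedure says that women who test HIV negative are those for whom "they provide verbal consent for PrEP initiation and collection of subsequent refills". Its list of criteria for the TOPAZ standard-of-care arm ends with verbal consent, without saying to what.

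**Analysis.** Data Analysis for Aim 2 plans an intent-to-treat analysis from the KP program database. It describes the GEE risk difference as one among people initiating PrEP in intervention versus comparison suburbs, and concludes: "Overall, this analysis framework permits causal attribution". The sample-size section counts enrolled women: 25 per intervention suburb, 100 in that arm.

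**The concern.** Randomizing suburbs makes the two sets of suburbs comparable, and with them all women who start PrEP there. It does not make subsets comparable when those subsets form after allocation is known and by different routes. Here one arm has an opt-in step that follows disclosure of the pharmacy option and the vouchers. The other arm is recruited without that information. If women who take up an offer tied to refills are more likely than decliners to return anyway, an enrolled-only comparison shows a difference even when the intervention does nothing.

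Covariate-constrained randomization balances suburbs, not the women who opt in. The permutation test and the GEE model take the analysed women as given, so neither corrects this. At stake are the primary retention contrast and the unqualified causal statement attached to it. The Discussion's limitations do not mention recruitment bias.

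**Working it through.** **Step 1. Which women are analysed?**

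| Section | Population implied |
|---|---|
| Data Analysis for Aim 2 | People initiating PrEP in the suburbs, from the KP program database |
| Overview of PrEP Services in the KP Program | Routine forms exist for every SW who initiates PrEP, so such a set could be built |
| Recruitment, intervention suburbs | Interested initiators who consent to TOPAZ |
| Procedures, standard-of-care arm | Women enrolled under a verbal-consent criterion with no stated object |
| Sample Size and Power Calculations | 100 enrolled women in the intervention arm |

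The first two rows point to all initiators and the last three to enrolled women. No sentence settles the matter.

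**Step 2. The plan's own power figure.** Inputs from the sample-size section: 4 suburbs per arm, 25 women per suburb, ICC 0.12, 14% versus 50%. Two-sided alpha 0.05 and 25 women per control suburb are my assumptions, since neither is stated.

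- Design effect = 1 + 24 × 0.12 = 3.88; effective n per arm = 100 / 3.88 = 25.8.
- Pooled two-proportion formula: z = [0.36 × √25.8 − 1.96 × √(2 × 0.32 × 0.68)] / √(0.14 × 0.86 + 0.50 × 0.50) = (1.828 − 1.293) / 0.609 = 0.88, so power is 81.0%.
- The other two scenarios give 80.4% (10% versus 44%) and 79.7% (30% versus 68%).

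The stated 80% reproduces by this formula. The recruitment point does not depend on it; it is the baseline for step 4.

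**Step 3. Spurious difference if only consenters are analysed.** Suppose no true effect and 14% retention among all initiators in both arms. Let c be the share consenting in intervention suburbs and r_d the retention among decliners. Both are assumed, as the article gives neither. Consenter retention is (0.14 − (1 − c) × r_d) / c, and the spurious difference is that value minus 0.14.

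| c | r_d = 10% | r_d = 5% | r_d = 0% |
|---|---|---|---|
| 90% | +0.4 points | +1.0 | +1.6 |
| 70% | +1.7 | +3.9 | +6.0 |
| 50% | +4.0 | +9.0 | +14.0 |

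Example: c = 0.7 and r_d = 0.05 give (0.14 − 0.3 × 0.05) / 0.7 = 17.9%, a difference of +3.9 points. The table treats control women as representative of all initiators. All entries are positive because every r_d is set below 14%; decliners retained better than 14% would reverse the sign.

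**Step 4. Price of analysing all initiators.** Suppose consenters reach 50% and decliners stay at 14%. Intervention-suburb retention is then c × 0.50 + (1 − c) × 0.14.

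| c | Retention, all initiators | Power, 25 per suburb analysed | Power, 25 enrolled, so 25/c initiators per suburb |
|---|---|---|---|
| 90% | 46.4% | 73% | 74% |
| 70% | 39.2% | 54% | 57% |
| 50% | 32.0% | 33% | 37% |

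The last column gives both arms 25/c women per suburb. At c = 0.7 that is 35.7 per suburb and an effective n of 4 × 35.7 / (1 + 34.7 × 0.12) = 27.7. With an ICC of 0.12 the extra women recover little.

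**The case against.** Four stronger readings are tempting, and the article does not support them.

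- **That decliners are dropped from the analysis.** This is not stated. The analysis section names people initiating PrEP and uses a database fed by routine forms on every initiator. On that reading decliners are counted and the consent-step bias does not arise. This stands, so the finding is conditional.
- **That controls pass no consent step.** The standard-of-care section speaks of women enrolled in TOPAZ and lists verbal consent as a criterion. Ethical Considerations says all participants are informed about the study and consent. Control consent could therefore be consent to TOPAZ. What remains is the difference in information: control women are not explicitly told of the intervention, and no interest step is described for them.
- **That the bias certainly favours the intervention, by a known amount.** Neither sign nor size can be derived from the article. Enrolment obliges nobody to use a pharmacy, since KP clinic refills stay open to participants, so acceptance could be high. At 90% consent the table gives at most +1.6 points.
- **That the vouchers drew in extra PrEP initiators.** The text informs women who have initiated or are initiating PrEP, which places the selection at TOPAZ consent.

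It can also be said that this is a pilot powered only for large effects, and that progression is judged qualitatively, with trial outcomes one input to two of four indicators. That limits the consequences for the go/no-go decision. It does not support the unqualified causal sentence.

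**Conclusion.** The point holds in conditional form. The article defines the aim 2 population in two incompatible ways, and recruitment after open allocation differs between arms in the information given and in the interest step described. If only enrolled women are analysed, the comparison is open to recruitment bias that the planned methods do not remove, and the causal-attribution sentence is not supported. If all initiators are analysed, this particular bias goes, but the eligibility and sample-size text then describes a different set.

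Under the assumptions of step 3, the possible spurious difference is about +0.4 to +14 points. Even the upper end is well below the 36-point design effect, so this bias alone would not produce a difference of that size. It is large enough to matter for the estimate. A reader should not infer that bias has been shown to be present.

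**What to change.** 1. In Data Analysis for Aim 2, define the intent-to-treat set as all FSWs who meet criteria (1) to (3) and initiate PrEP at the outreach clinics of the 8 suburbs within one common calendar window. Take them from KP program records whether or not they enrolled in TOPAZ, subject to ethics approval for using decliners' routine records.
2. Keep the enrolled-only comparison as secondary, labelled as open to recruitment bias.
3. State what control women consent to.
4. Report initiations, offers, refusals and enrolments by suburb, as far as recorded.
5. If decliners' records cannot be used, remove or qualify the causal-attribution sentence and list recruitment bias as a limitation.

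**Cost.** The change concerns the analysis set, not trial conduct. Data collection ended in May 2025 and the analysis is planned for February 2026, so the definition should be fixed before that analysis. The work is a records extraction plus whatever approval is needed; women who refused TOPAZ may require more than a notification. The effect is diluted by decliners, and on the step 4 assumptions power falls from 81% to about 73%, 54% or 33% at 90%, 70% or 50% consent. The article should say so.
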